### Intervention

Using focus groups of women with and without CC screening experience, and a focus group of male partners, we collected formative data to adapt the *Game Changer* intervention for the context of CC. A key difference revealed by these data between the HIV context and that of CC is that internalized stigma did not appear to be an impediment to CC screening per se, but rather stigma, fears, and worries acted more as barriers to biopsies and treatment, and to sharing one’s screening result, once a woman learned that she was positive for the sexually transmitted human papillomavirus and at risk for CC. Support from male partners for screening and treatment was also cited as important, and men who had some basic level of knowledge about CC seemed largely supportive of women being screened.

The adapted intervention consists of 7 workshops. *Workshop 1* focuses on *addressing fears and concerns related to CC risk and use of self-compassion and peer support to overcome these fears*, as well as introducing the overall vision for empowering women to become change agents for CC prevention and treatment. With participants feeling more supported, *Workshop 2* focuses on *building skills and decision-making for sharing one’s personal CC screening experience*, knowing to whom to disclose and when and how to initiate and navigate disclosure and conversations about CC. *Workshop 3* builds skills and motivation for *healthy living* so that their own behavior (e.g., good nutrition, periodic VIA screens) is consistent with the behavior they encourage in others, as well as learning facts and myths related to CC to facilitate accurate CC screening advocacy. *Workshop 4* introduces the concept of a social network and how one’s network can serve as a tool for CC prevention advocacy and dissemination of CC-related information. *Workshops 5 and 6* focus on the skills needed for successful *CC-related advocacy*, including strategies for how to start conversations about CC and to keep these discussions going, as well as learning effective communication skills (e.g., reflective listening, paraphrasing, open-ended questions). *Workshop 7* inspires a *commitment to ongoing CC advocacy* through peer solidarity and support. The workshops will be conducted using a structured facilitator manual, in the predominant local languages of Samia and Lusoga, by two trained women from Namayingo who have experience being screened for CC. Using principles of compassion-focused therapy [27], the workshops will be administered in a group format to facilitate the use of *sharing of experiences* to build support, solidarity, and motivation among participants; *group problem-solving* and *role playing* to build skills and self-efficacy; *setting personal goals* regarding healthy living, disclosure, and advocacy; and homework to reinforce practice of new skills and generate personal experiences to be processed in the workshops. The seven workshops will be conducted weekly over 2 months, and each workshop will last 2 h. Participants will receive 30,000 Uganda shillings (~US $8) for attending each workshop to cover transport costs.

#### Facilitator training, supervision, and fidelity monitoring

The facilitators will be trained by the senior investigators over 3 days. The training will include reviewing the manual, objectives for each workshop, step-by-step scripts and the key points to emphasize, and role playing and mock implementation of core exercises. Training will cover group facilitation, building rapport with and among participants, reflective listening, and dealing with group conflict. The supervisor of the facilitators will observe the implementation of each of the workshops to provide feedback and further training as needed during weekly supervision. To monitor implementation fidelity, the supervisor will complete a rating form after each session to record if objectives were met, exercises completed, level of participant engagement, difficulties encountered, and areas to improve.

### Measures

Assessments will be administered at baseline and 6-month follow-up, in the local languages, either Samia or Lusoga, depending on the preference of the participant. Assessments include a standard survey (index and alter participants) and social network assessment (index participant only); the assessment of the index participant will last about 60 min while just 20 min for the alter. The assessment will be administered using Network Canvas computer-assisted software. The constructs being measured are listed in Table 1; measures will be translated into Samia and Lusoga using standard translation/backtranslation methodology. CC screening and treatment utilization will be verified with abstracted medical chart data. Participants will receive 30,000 Uganda shillings (~US $8) for each completed assessment to cover transport costs.

**Table 1 Tab1:** Constructs to be assessed

Constructs	Instrument
***Primary outcome***	
CC screening: index and alter	Self-report; chart abstraction
***Secondary outcomes***	
Receipt of CC-related treatment (e.g., thermal therapy; chemotherapy; radiation), if warranted: index and alter	Self-report; chart abstraction
Healthy living behaviors (condom use, diet, alcohol use, CC rescreening): index and alter	Developed in-house
Engagement/receipt of CC prevention and treatment advocacy: index and alter	Developed in-house
***Potential mediators***	
Internalized CC stigma: index	Kalichman et al. [28] adapted
Disclosure of CC screening and treatment results: index and alter	Developed in-house
Attitudes towards women with CC: index and alter	Developed in-house
Self-efficacy (adherence, disclosure, advocacy): index and alter	Chesney [29] adapted
CC-related knowledge: index and alter	Developed in-house
***Covariates/potential moderators***	
Demographics (age, education, work status, income, relationship status): index and alter	Developed in-house
Social support: index and alter	Moser et al. [30] adapted
Enacted CC stigma/discrimination: alter	Berger et al. [31] adapted

#### Social network assessment

Using Network Canvas software, each index participant will list 12 female adult alters (which is adequate to capture structural and compositional variability) [32] with whom they interact most. For each alter, we will gather information to assess *network composition* (e.g., age, HIV status, relation to index; perceived history with CC screening and treatment; knowledge of index’s CC screening and treatment). Index participants will report how well each alter knows each other alter to assess *network structure* (e.g., density or connectedness among alters). *To assess CC advocacy*, we will ask the index participant if they have encouraged the alter regarding CC screening and/or treatment, risk reduction behaviors (condom use), and any perceived resulting action (e.g., alter sought VIA screening). At follow-up, we will determine whether listed alters are the same or unique from those listed at baseline, which allows for both sequential cross-sectional analyses and longitudinal analyses of alter data. Our prior research shows that alter behaviors such as diagnosis disclosure and health-seeking behaviors can be accurately reported by index participants [33].

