## Methods

### Study design

This study will pilot test a social network-based group intervention that aims to empower and mobilize women who have been screened for CC to advocate for CC screening and treatment in female members of their social network (referred to as “alters”). We will pilot the intervention in a randomized controlled trial of 40 women who have been screened for CC (referred to as index participants), with 20 randomly assigned to receive the intervention (in two groups of 10) and 20 to the wait-list control [(each evenly stratified by age (under and over age 35) and history of CC-related treatment)]. Individual randomization entails risks for contamination, but statistical models suggest that ≥ 30% of the control arm must receive the equivalent of a full-strength intervention to result in meaningful contamination [24]. We opted for the wait-list control rather than an attention control, because this provides clearer findings for policy makers when considering intervention effects, and adequate control for attention may not be feasible given the 2-h duration and group dynamics of the workshops. The control arm receives the intervention after the completion of month-6 follow-up assessments. There is no way to blind the participants on whether or not they receive the intervention; this could potentially influence the outcomes, as clients may feel more or less incentivized to perform well in light of whether or not they receive the intervention. We do not see a way to prevent this potential bias, nor a way to distinguish such effects from actual intervention effects, but this limitation will be cited in reports of study findings. Data will be collected at baseline and month 6 from index participants and up to three alters of each index participant (max. total = 120 alters) who have not previously screened for CC. The primary outcome is alter CC screening over the 6-month follow-up period; secondary outcomes are index participant reported engagement in CC screening advocacy, internalized CC stigma, and disclosure of CC screening experience.

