### Statistical analysis

To assess feasibility and acceptability, we will examine recruitment (percent of screened women and social network members who are approached to participate, decide to enroll), retention, workshop attendance, and participant feedback elicited in the process measures. To assess intervention effects on alter CC screening, *w*e will use an intent-to-treat approach. In addition to comparing the arms at each time interval (baseline, month 6), we will apply logistic generalized mixed models to our repeated-measure data to examine intervention effects, using an indicator for study arm, and time by arm interaction to indicate whether change differs between the arms. We will use imputation for item nonresponse and attrition weights to account for nonrandom dropouts using logistic regressions; if dropout is random, analyses will incorporate design effects. We will explore the sensitivity of significance levels and conclusions to a range of plausible ICC values (.005 to .05) for the outcomes. We will control for and examine interaction effects with intervention process variables (e.g., number of workshops completed) and characteristics of the index participant (e.g., age), as well as the alter (e.g., position in the network, knowledge of index participant’s CC risk).

We will explore factors that may mediate the intervention effects on the primary outcomes among variables targeted by the intervention*,* such as internalized CC stigma, disclosure (percentage of alters disclosed to), and engagement in CC screening advocacy. The sample size may be too small to do mediation analysis, but we will examine how potential mediators are associated with the primary outcomes and treatment condition using bivariate statistics.

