## Discussion

This study will conduct a randomized, controlled pilot evaluation of a social network-based group intervention designed to empower women who have screened for CC to advocate for CC screening and early treatment among women in their social networks. To our knowledge, no published study has used a network-driven approach and empowerment of screened women (some of whom have also been treated for CC risk) as change agents to increase CC screening and treatment, let alone in Africa. This is one of the few network-driven interventions to use social network data not only to evaluate effects on the behavior of network members but also to inform intervention strategies for targeting advocacy to bridging and popular network members, which may optimize the knowledge and support transfer for CC protective behaviors throughout a network. With essentially every family affected by CC risk in high-prevalence settings like Uganda, the intervention can dramatically impact the mortality and morbidity of CC through widely disseminated and targeted advocacy. This study will inform a future, larger controlled intervention trial, including a more extensive evaluation of effects on network members and the community. If successful, this intervention model has the potential to not only impact uptake of CC screening and treatment but also to establish a paradigm that can be applied to other health conditions.

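### The month-6 network list appears to be elicited afresh, so index-reported advocacy and disclosure may rest on names chosen after randomisation; ask about the 12 baseline women first.

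*Protocol article*

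**What the plan says.** All references are to the protocol article.

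- **Measures.** Assessments take place at baseline and month 6: "Assessments include a standard survey (index and alter participants) and social network assessment (index participant only").
- **Social network assessment.** At this assessment "each index participant will list 12 female adult alters", the rule being those "with whom they interact most". Advocacy is recorded for each listed woman: "we will ask the index participant if they have encouraged the alter regarding CC screening and/or treatment". On the second visit: "At follow-up, we will determine whether listed alters are the same or unique from those listed at baseline". The section adds that this permits both repeated cross-sectional and longitudinal analyses of the alter data.
- **Study design.** The "secondary outcomes are index participant reported engagement in CC screening advocacy, internalized CC stigma, and disclosure of CC screening experience".
- **Statistical analysis.** Advocacy and disclosure return as possible mediators, with disclosure given as "disclosure (percentage of alters disclosed to").
- **Intervention and Discussion.** Workshop 4 presents the woman's network as a means of advocacy, and the Discussion says network data also serve to "inform intervention strategies for targeting advocacy to bridging and popular network members". Controls receive the workshops only after their month-6 assessment.

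**The concern.** A check on whether month-6 names match the baseline names is needed only if names are elicited again. With the baseline roster simply carried forward, there would be nothing to determine. The article does not say that a baseline woman who is not named again is still asked about.

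On that reading, the set of women over whom index-reported advocacy and disclosure are counted is formed after randomisation. By then the intervention arm has had seven workshops that encourage conversations about cervical cancer within the network, and the control arm has had none. The naming rule is frequency of contact, which such conversations could alter. Weekly meetings in groups of 10 screened women could also bring fellow participants onto the list. Randomisation does not protect a comparison whose denominator the intervention may change.

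Two secondary outcomes, which are also candidate mediators, are at stake. The pilot is meant to supply effect sizes and other parameters for a larger trial, so a distorted advocacy or disclosure effect would carry into that design.

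**Working it through.** **Inputs from the article.** List size 12; up to 3 enrolled alters per index woman, drawn from the baseline list among women who know of her screening (Participants). No turnover rate is given, so every turnover figure below is an assumption.

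**Plan's own figure.** The article has no calculation for these outcomes. Its only one concerns alter screening and reproduces: 120 × 0.9 / 2 = 54 alters per arm; 54 / (1 + 2 × 0.01) = 52.9, stated as 53. The network list is not an input, so this figure is untouched.

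**Step 1: shift in a cross-sectional percentage.** Suppose k of 12 names are replaced, a share d of the dropped women and a share q of the added women count as disclosed to (or advocated to), and nothing changes for anyone else. Then

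shift in percentage points = 100 × k(q − d) / 12.

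*One woman.* She has told 6 of 12 (50%). She drops 3 untold women (d = 0) and names 3 she had already told (q = 1): 100 × 3(1 − 0) / 12 = 25. The list reads 9/12 = 75%, with no new disclosure. This is the most unfavourable swap of three names.

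*Average over women.* Assume 40% at baseline and dropped women typical of the list (d = 0.4).

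| k replaced | q = 0.6 | q = 1.0 |
|---|---|---|
| 2 | 43% (+3) | 50% (+10) |
| 4 | 47% (+7) | 60% (+20) |
| 6 | 50% (+10) | 70% (+30) |

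**Step 2: from shift to arm difference.** The spurious difference is the shift in the intervention arm minus the shift in the control arm. If both arms change their lists alike, it is zero. If only the intervention arm changes, it equals the bracketed figure, 3 to 30 points over this assumed range.

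**Step 3: the longitudinal alternative.** In the one-woman example 9 baseline women are named again, 6 of them told: 6/9 = 67% at both visits, a change of 0. Comparing re-listed women with themselves therefore removes the substitution artefact. The 9 are still a subset defined at month 6. If being named again depends on whether the index has been talking to that woman, and this differs by arm, a selection effect remains.

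**Step 4: index reports on enrolled alters.** If k names drop at random, the chance that all 3 enrolled alters stay listed is C(9,k)/C(12,k):

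- k = 2: 36/66 = 55%
- k = 4: 126/495 = 25%
- k = 6: 84/924 = 9%

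This concerns only the index's month-6 answers about those women.

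**Step 5: what does not depend on the list.** Enrolled alters are surveyed themselves at both visits (Measures). Table 1 lists receipt of advocacy for index and alter, and screening by self-report and chart. None of this requires the index to name the alter again.

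**The case against.** The strongest reply is that the interview procedure is inferred. The article does not describe the month-6 script, and a condensed article may leave to it whether the baseline roster is also shown. The investigators plainly expect turnover and plan to match names, and the longitudinal analysis disposes of the swap example. The naming rule is contact, not having discussed screening, so a shift that differs by arm is conjecture. The percentage form of disclosure appears only in the mediator text, which falls back on bivariate statistics.

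Much of this stands. That the list differs by arm is a possibility, not a finding, and no magnitude can be taken from the documents. What remains is that the one sentence describing month 6 presupposes a new list, and that each analysis it offers uses either that list or the part of it overlapping baseline. The attrition weights in Statistical analysis are for dropouts; an alter left off the list of a retained index woman is not one.

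A reader might infer more: that advocacy can no longer be related to screening for enrolled alters who are not re-listed. The documents do not support that. Those alters report advocacy received and have their own screening data, so the link survives; only the index's account of it would be missing. Nor would new disclosure to them be hidden, because they were selected as already knowing of the index's screening.

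**Conclusion.** The point holds as a modest one. As described, index-reported advocacy and the disclosure percentage may be computed on a list formed after randomisation and after the workshops. The cross-sectional comparison can then mix changed behaviour with changed naming, and the longitudinal comparison is confined to women named twice.

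The size and direction of any bias are unknown. The 25-point example and the 3 to 30 point range rest wholly on assumed turnover, and the range becomes an arm difference only if turnover of that kind occurs in one arm alone. The conclusion also rests on reading the follow-up sentence as fresh elicitation, which is implied and not stated outright. It would be tempting to conclude that the trial's main result is compromised; it is not, because alter screening comes from the alters' own survey and charts. This is an inexpensive improvement to secondary outcomes of a pilot.

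**What to change.** At month 6, pre-load each woman's baseline roster and ask the advocacy, disclosure and perceived-action questions about all 12 baseline women, including the enrolled alters, whether or not she would name them again. Only then elicit new names by the same contact rule.

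Make the main arm comparison of index-reported advocacy and disclosure on the fixed baseline roster. Report newly named women separately: a fixed roster alone would miss advocacy to new contacts, which this intervention may well generate. The network-change analyses that the investigators want remain possible.

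If the interview script already does this, a sentence saying so, and naming the roster as the basis of the two outcomes, is enough. Otherwise the cost is a script change and some added minutes for women whose network has changed, on top of an index assessment of about 60 minutes. No extra visit or staff is needed.

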### Statistical analysis

To assess feasibility and acceptability, we will examine recruitment (percent of screened women and social network members who are approached to participate, decide to enroll), retention, workshop attendance, and participant feedback elicited in the process measures. To assess intervention effects on alter CC screening, *w*e will use an intent-to-treat approach. In addition to comparing the arms at each time interval (baseline, month 6), we will apply logistic generalized mixed models to our repeated-measure data to examine intervention effects, using an indicator for study arm, and time by arm interaction to indicate whether change differs between the arms. We will use imputation for item nonresponse and attrition weights to account for nonrandom dropouts using logistic regressions; if dropout is random, analyses will incorporate design effects. We will explore the sensitivity of significance levels and conclusions to a range of plausible ICC values (.005 to .05) for the outcomes. We will control for and examine interaction effects with intervention process variables (e.g., number of workshops completed) and characteristics of the index participant (e.g., age), as well as the alter (e.g., position in the network, knowledge of index participant’s CC risk).

We will explore factors that may mediate the intervention effects on the primary outcomes among variables targeted by the intervention*,* such as internalized CC stigma, disclosure (percentage of alters disclosed to), and engagement in CC screening advocacy. The sample size may be too small to do mediation analysis, but we will examine how potential mediators are associated with the primary outcomes and treatment condition using bivariate statistics.

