**Methods:**

Forty adult women (index participants) who have recently screened for CC will be recruited, 20 of whom will be randomly assigned to take part in the intervention and 20 to the wait-list control. Each index participant will be asked to recruit up to three female social network members (i.e., alters; maximum total = 120 alters) who have not screened for CC to participate in the study. Assessments (survey and chart abstraction) will be administered at baseline and month 6 to index and alter participants. The primary outcome is CC screening among participating alters, with a secondary outcome being engagement in CC prevention advocacy among index participants. Repeated-measure multivariable regression analyses will be conducted to compare outcomes between the intervention and control arms.

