### Participants

Women are eligible to enroll as index participants if they are age 18 years or older, have screened for CC within the past year, have stable health status (i.e., not in end stages of disease), and shared their CC screening experience with at least one alter who is perceived to not have screened for CC in the past 3 years. Alter participants are eligible if they are at least 18 years of age, are recruited by an index participant, and report never being screened for CC.

Index participants will be recruited through the RHHJ database of women who have received CC screening and referral from Buyinja and Banda providers who have screened women for CC. An RHHJ staff member or health center provider will inform eligible women of the study, and those who express interest in participating will be referred to the study coordinator for formal eligibility screening and implementation of consent procedures. Women who provide written informed consent will then be administered the baseline assessment and be randomly assigned to the intervention or control arm. To recruit alters, we will use data collected from the baseline survey assessment of female social network members to randomly select 5 alters who know the participant’s CC screening experience (or as many as there are if < 5) and ask the participant if she is comfortable asking 3 of these alters to participate. The index participant will be asked to call each selected alter at the end of the interview to describe the study in the presence of the coordinator, who will schedule a study visit for alters who express interest in participating. If an alter refuses or cannot be reached, a replacement will be randomly selected from the list of alters who know the index participant’s CC screening experience.

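### The time-by-arm interaction named for alter screening cannot be estimated, because every enrolled alter is unscreened at baseline; the month-6 arm comparison should be named as primary

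*Protocol article*

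**What the plan says.** **Outcome.** Study design states: "The primary outcome is alter CC screening over the 6-month follow-up period".

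**Who is followed.** Participants admits only alters who "report never being screened for CC". Study design says the same, describing data from "up to three alters of each index participant (max. total = 120 alters) who have not previously screened for CC".

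**When.** There are two time points. Measures states: "Assessments will be administered at baseline and 6-month follow-up".

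**Model.** In Statistical analysis the text opens with "To assess intervention effects on alter CC screening" under intent to treat. It then applies logistic generalized mixed models to the repeated measures, "using an indicator for study arm, and time by arm interaction to indicate whether change differs between the arms". The same sentence begins by saying that the arms will also be compared at each time point, baseline and month 6. The abstract mentions only the modelling: "Repeated-measure multivariable regression analyses will be conducted to compare outcomes between the intervention and control arms".

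**Power.** Sample size rests on a simple difference in the proportion of alters screened during follow-up: 5% in controls, a detectable difference of 19 percentage points, and an effective 53 per arm.

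**The concern.** A time-by-arm interaction in a logistic model compares the arm odds ratio at month 6 with the arm odds ratio at baseline. Eligibility fixes the baseline outcome at 0 in both arms, so the baseline odds ratio is 0/0 and the difference between the two log odds ratios has no defined value. The stated model conflicts with the stated eligibility rule, so this is not a detail left for an analysis plan to supply.

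An analyst who follows the text literally will get either a convergence failure or a coefficient with an enormous standard error. A Wald test of that coefficient says nothing about the intervention, however large the true effect. The baseline half of the planned arm comparison is uninformative too, since it compares 0 with 0. The trial's stated purpose is to supply a preliminary effect size for a larger trial, so it matters that the term designated to carry the effect is one that can be estimated.

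**Working it through.** **Step 1. Reproduce the plan's figures.** Inputs from Sample size: 120 alters, 10% attrition, ICC 0.01, 5% screened in controls, 19-point difference, 80% power, alpha 0.05 (taken as two-sided; the article does not say). Cluster size is three alters per index participant.

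- Alters per arm after attrition: 120 × 0.9 / 2 = 54.
- Design effect: 1 + (3 − 1) × 0.01 = 1.02. Effective n: 54 / 1.02 = 52.9 (stated 53).
- Two-proportion test, 5% v 24%, 53 per arm, no continuity correction: power 0.802 (stated 0.80).
- Arcsine effect size: 2·asin(√0.24) − 2·asin(√0.05) = 0.573 (stated 0.57).

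The stated power therefore belongs to a two-group comparison of screening by month 6.

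**Step 2. Illustrative data at the planning rates.** 54 alters per arm, all 0 at baseline. At month 6, 3/54 (about 5%) are screened in control and 13/54 (about 24%) in intervention.

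**Step 3. Fit arm, time and arm × time by maximum likelihood (no random effect).**

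| Iterations | Intercept | SE of interaction | p |
|---|---|---|---|
| 5 | −6.6 | 3.2 | 0.60 |
| 10 | −11.6 | 37.9 | 0.96 |
| 20 | −21.6 | 5,626 | 1.00 |
| 30 | −31.6 | 834,942 | 1.00 |

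The intercept drifts towards minus infinity. The log-likelihood is −41.3905 with the interaction and −41.3905 without it. It keeps that value when the interaction is fixed at −3, −1, 0, 1, 2, 3 or 5. The data carry no information on the term.

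**Step 4. Add a random intercept for the index participant** (18 index participants with 3 alters each per arm, same totals). The profile log-likelihood is −41.2783 at every interaction value tried from −5 to +8. It is again flat, so the mixed model does not supply the missing baseline information.

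**Step 5. Month-6 contrast in the same data.**

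- Log odds ratio: ln[(13/41) / (3/51)] = 1.68.
- SE: √(1/13 + 1/41 + 1/3 + 1/51) = 0.67; p = 0.012.
- Risk difference: 13/54 − 3/54 = 10/54 = 18.5 percentage points.

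**Step 6. Would penalisation rescue the interaction?** For this saturated model a Firth-type fit adds 0.5 to each cell.

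- Month-6 contrast: ln[(13.5/41.5) / (3.5/51.5)] = 1.57, SE √(1/13.5 + 1/41.5 + 1/3.5 + 1/51.5) = 0.64.
- Interaction: the same 1.57, but the two empty baseline cells add 2 × (1/0.5 + 1/54.5) = 4.04 to the variance. SE = √(0.40 + 4.04) = 2.11, z = 0.74.

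The baseline part alone gives an SE of at least √4.04 = 2.01. Significance would need a log odds ratio above 1.96 × 2.01 = 3.94. The planned effect is ln[(0.24/0.76) / (0.05/0.95)] = ln 6.0 = 1.79. In 20,000 simulated trials with independent alters, the penalised interaction was significant in 0%, against about 80% for the penalised month-6 contrast.

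**Step 7. Sparse control events at month 6.** Expected: 54 × 0.05 = 2.7. Chance of none: 0.95^54 = 0.063. With 80 alters enrolled (36 per arm after attrition): 0.95^36 = 0.158. These treat alters as independent.

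**The case against.** **The month-6 comparison is already planned.** This is the strongest point on the other side, and it stands. With all alters at 0 at baseline, the month-6 arm comparison is exactly the intervention effect on screening over follow-up. A reader might infer that the primary question goes unanswered, or that a real effect would be reported as null. The article does not support either: an estimable answer is in the plan, and an interaction with a standard error in the thousands would be noticed rather than read as evidence of no effect. What remains is that this comparison is presented alongside the model, is not designated primary, and has no clustering adjustment attached to it by name, while the interaction is the term given the job of showing the effect.

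**The sample size.** A reader might also infer that the power calculation is wrong. It is not. It reproduces, and it matches the month-6 comparison; it only fails to match the interaction.

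**The model has other uses.** Under Social network assessment, index participants report perceived screening for 12 listed women at both visits, and those women need not be unscreened. Advocacy and stigma can also vary at baseline. The interaction model can serve there. This does not help enrolled-alter screening, for which Statistical analysis introduces it.

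**Baseline might not be all zeros.** Eligibility is by self-report and screening is verified against charts, so a few earlier screenings could come to light. They would be eligibility misreports, and an interaction resting on a handful of them would be very unstable.

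**It is a pilot.** This lowers the stakes of any significance test, but the aim of estimating an effect size still needs an effect term that exists.

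**Conclusion.** The point holds in a limited form. For enrolled-alter screening, the time-by-arm interaction has no finite or unique maximum-likelihood estimate, with or without a random intercept for the index participant, and the baseline arm comparison is 0 v 0. The month-6 comparison in the same sentence is estimable, answers the primary question, and carries the stated 80% power at 5% v 24%. The fault is a model term that does not fit this outcome, together with no statement of which analysis is primary. No data and no part of the sample size are compromised.

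That the interaction is unidentified follows from eligibility and does not depend on the month-6 rates. The numerical illustrations assume the article's 5% and 24% and 54 alters per arm. The mixed-model check used one illustrative allocation of events with an index-level random intercept only.

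**What to change.** In Statistical analysis, for screening among enrolled alters:

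1. Name as primary the arm contrast in screening by month 6, from a logistic mixed model or GEE with clustering by index participant, and report the risk difference with its 95% confidence interval.
2. Remove the time and time-by-arm terms and the baseline arm comparison for this outcome.
3. Keep the repeated-measures interaction model only for outcomes that vary at baseline, and say which these are.
4. State a fallback for few or no control events. A penalised-likelihood fit is sensible. An exact test may cost power: at 54 per arm, 5% v 24% and ignoring clustering, exact power is 0.75 for Fisher's test against 0.84 for the pooled z-test.

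Align the abstract's sentence on repeated-measure regression with this. The cost is wording only: the sample size, visits and data collection stay as they are.
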